### Protocol stopping rules

Due to the fact that this protocol is designed as a pilot study of spironolactone therapy, we have not set predetermined protocol stopping rules for clinical efficacy. However, as described above, the occurrence of excess life-threatening or serious adverse events (such as severe hyperkalemia or renal insufficiency) is possible and the frequency and distribution of these events in each treatment group will be monitored closely. Serious adverse events and unexpected adverse events will be reviewed with the help of the Data Safety and Monitoring Board (DSMB) to determine the relationship of these events to the current protocol.

### Human participant protection

#### Rationale for participant selection

Criteria for exclusion or withdrawal from the study are based on the presence of other disease processes that may interfere with the interpretation of our results or situations that may be harmful to the participants. Individuals of both genders and all races will be considered for inclusion in this study. Cognitively impaired and institutionalized persons unable to provide written informed consent will not participate in this study.

#### Participation of children

Children under the age of 18 will be excluded from this protocol because of differences between adults and children with regards to functional classification and exercise capacity at the time of PAH diagnosis [65]. In addition, a substantially higher proportion of pediatric patients demonstrate acute vasoreactivity at the time of right heart catheterization compared to adults [65]. These differences would add additional heterogeneity to the study population and therefore could potentially obscure the effects of the study drug on exercise capacity, clinical worsening, RV function and vascular inflammation.

#### Participation of pregnant women

Because of potential adverse effects on the fetus, pregnant participants will be excluded from the study. In addition, women of childbearing potential must agree to use adequate contraception (hormonal, barrier method of birth control, or abstinence) prior to and for the duration of study participation. Female participants with childbearing potential will be regularly assessed throughout the study. In the event of a positive pregnancy test, the participant will be immediately informed of this result, the study drug will be discontinued, and the participant will be removed from the study.

### Risks and discomforts

#### Risks associated with spironolactone therapy

The most significant risks associated with spironolactone therapy include hyperkalemia, renal insufficiency, hypovolemia and gynecomastia with or without breast pain. In a large trial of patients with NYHA class III and IV LV heart failure (the mean dose of spironolactone was 26 mg and dose titration up to 50 mg daily), the incidence of severe hyperkalemia (>6 mEq/L) was not significantly different between the spironolactone treatment group (2%) and placebo (1%) but the median potassium concentration did increase by 0.30 mmol/L in the spironolactone-treated group [15]. The median creatinine concentration also increased (0.05 to 0.10 mg/dL) in the spironolactone-treated group. The risk of hyperkalemia while on spironolactone therapy is increased in the presence of renal insufficiency, concurrent use of ACE inhibitors or angiotensin receptor blockers, potassium-sparing diuretics or NSAIDs [66]. Precautions that will be taken include: participants will be counseled to avoid foods high in potassium and to avoid concurrent use of NSAIDs; patients taking ACE inhibitors, angiotensin receptor blockers, or potassium-sparing diuretics will be excluded from the study; participants will undergo frequent monitoring of serum potassium, creatinine and blood urea nitrogen; cessation of the study drug when serum potassium ≥6 mEq/L or when it remains ≥5.3 mEq/L on two occasions; and cessation of the study drug when creatinine increases by >50% of baseline value.

Gynecomastia in men and painful breast enlargement in women may occur in participants treated with spironolactone and appear to be related to dose and duration of therapy [67-69]. The Randomized Aldactone Evaluation Study reported incidences of gynecomastia and breast pain in 9% and 2% of spironolactone-treated patients, respectively. This was significantly different from placebo and led to discontinuation of the study drug in 2% of spironolactone-treated patients in this trial [15]. In the majority of cases, gynecomastia and breast pain subside with cessation of the drug [68,70]. Prior to initiation of the study drug and throughout the trial during follow-up visits, participants will be asked about the presence of breast pain and, in male patients, the development of gynecomastia. If while on the study drug a participant develops significant breast pain or gynecomastia then the study drug will be discontinued. Additional side effects reported with spironolactone therapy and related to its progesteronal and anti-androgenic activity include menstrual irregularities (amenorrhea, postmenopausal bleeding), decreased libido and erectile dysfunction [67-69]. These also appear to be dose related and typically resolve upon drug cessation [69,71].

#### Risks associated with venipuncture

Blood draws throughout the study are well within the NIH Clinical Center policy (that is, the amount of blood drawn for research purposes from participants 18 years of age or older will not exceed 550 mL or 10.5 mL/kg, whichever is smaller, over any eight-week period). Standard precautions for obtaining human blood samples will be taken. Transient discomfort and minor bruising may occur at the phlebotomy site. Vasovagal symptoms can occur during blood drawing.

#### Six-minute walk test

The risks associated with a symptom-limited six-minute walk are minimal.

#### Cardiopulmonary exercise testing

Exercise testing is a safe procedure with experienced personnel. Conduction abnormalities or atrial/ventricular arrhythmias may occur during the test, requiring institution of advanced cardiovascular life support. The participant could also develop ischemic symptoms requiring intensive care unit monitoring and treatment.

#### Transthoracic echocardiography

There is no known risk from the ultrasound examination. The safety of echocardiography has been well established. Localized transient discomfort from the probe and irritation from the ultrasound gel may occur.

#### Magnetic resonance imaging and gadolinium contrast agent

MRI uses no ionizing radiation and is quite safe when performed on a properly screened population. Potential risks relate to the magnetic field’s effect on participants with implanted metal objects (such as cerebral aneurysm clips, cochlear implants). The magnetic field can cause twisting or movement of these objects thus causing harm to the patient. Also the radiofrequency power associated with MRI can potentially cause burns in patients with pacemakers or other implanted coiled wires. Participants will be screened for these objects and excluded as indicated. The scanner gradient performance (dB/dt limit) is set on an individual basis to avoid painful peripheral nerve stimulation. Precautions that will be taken include informing the participant of the possibility for peripheral nerve stimulation in the consent form; empirically using parameters that maintain gradient switching rates below the pain threshold; and audio feedback from the participant.

The NIH MRI Unit adheres to the Food and Drug Administration guidelines for radiofrequency power levels (specific absorption rate limits). The MRI scanner is operated at the Food and Drug Administration limits established for MRI in general applications. However, in cases of a damaged or dysfunctional surface coil, there is a small chance of local warming in the body. For safety purposes, participants are asked to report this sensation so scans can be modified or the integrity of hardware verified.

Participants may receive an intravenous injection of gadolinium chelate that is not to exceed 0.2 mmol/kg gadolinium per bolus injection and 0.4 mmol/kg gadolinium per examination. We will be adhering to the NHLBI polices regarding administration of gadolinium. Experience with a large number of patients has shown that these commercially available gadolinium chelates are safe [72-76] and without side effects in the majority (>98%) of patients. When side effects do occur, they are usually mild and transient. These include coldness in the arm during the injection, a metallic taste, headache and nausea. More severe reactions (shortness of breath, wheezing or hypotension) are extremely rare. More recently however, there have been reports of nephrogenic systemic fibrosis or nephrogenic fibrosing dermopathy associated with the use of gadolinium in patients with severe renal dysfunction [77]. The risk of these occurrences should be minimized through the use of a questionnaire form and an assessment of eGFR in all participants.

### Data and safety monitoring

#### Clinical monitoring plan

The principal investigator will monitor accrual and safety data as well as occurrence of any unusual or unpredicted complications. An independent DSMB established by the NHLBI will review symptom and outcome data at 6-month intervals to ensure participant safety and confirm that withdrawal criteria are observed. Study monitoring will be conducted by an outside consultant working under an agreement with the NHLBI to monitor aspects of the study in accordance with the appropriate regulations and the approved protocol. Stopping rules and withdrawal criteria have been established to ensure participant safety during the study. The DSMB may recommend early termination of the study for considerations of safety and efficacy. Accrual and safety data will also be monitored and reviewed annually by the Institutional Review Board.

#### Data management

The principal investigator will be responsible for overseeing entry of data into a password-protected electronic system and ensuring data accuracy, consistency and timeliness. On all study documents, participants will be identified by a participant number assigned at enrollment, and will not be identified by name. Data will be stored in locked cabinets and in a password-protected database until it is no longer of scientific value. Should we become aware that a major breech in our plan to protect patient confidentiality and trial data has occurred, the Institutional Review Board will be notified.

#### Adverse events and serious adverse events reporting

Adverse events reported under this protocol will be limited to those events that are possibly, probably or definitely related to the research described in this protocol.

Unanticipated problems that are either adverse events or non-adverse events will be reported within 7 calendar days of investigator awareness. The following items will also be reported to the NHLBI Institutional Review Board in summary at the time of Continuing Review: all unanticipated problems; any protocol-specific reporting requirements; and all protocol deviations, which in the opinion of the investigator require reporting.

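### The adverse event section reports only events already judged related, which contradicts the stopping-rules section, where relatedness is determined with the DSMB and events are monitored by arm

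*Protocol article*

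**What the plan says.** The section headed "Adverse events and serious adverse events reporting" opens with a restriction: "Adverse events reported under this protocol will be limited to those events that are possibly, probably or definitely related to the research". It names no recipient and makes no separate provision for serious events. Its second paragraph adds one route that does not mention attribution: "Unanticipated problems that are either adverse events or non-adverse events will be reported within 7 calendar days of investigator awareness". It then lists what goes to the Institutional Review Board in summary at Continuing Review.

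Protocol stopping rules discusses life-threatening or serious adverse events, with severe hyperkalemia and renal insufficiency as examples, and says that "the frequency and distribution of these events in each treatment group will be monitored closely". For events that are serious or were not expected, it then sets out a review: they "will be reviewed with the help of the Data Safety and Monitoring Board (DSMB) to determine the relationship of these events to the current protocol".

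Clinical monitoring plan says that the DSMB "will review symptom and outcome data at 6-month intervals to ensure participant safety and confirm that withdrawal criteria are observed", and allows it to recommend early termination.

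**The concern.** The two sections use relatedness in incompatible ways. One makes it the condition an event must meet before it is reported. The other treats it as a question to be answered, with the DSMB's help, once the event is in hand. An event that an investigator has already judged unrelated cannot be reconsidered if it was never put forward, nor can it be counted by treatment group.

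The matter is more than editorial in this population. Individual participant stopping rules acknowledges that clinical worsening may occur whatever the assigned treatment, so attributing an event to the underlying disease will often seem natural. A randomised placebo arm exists to separate drug from disease without relying on such case-by-case judgement. The background and discussion both say that no randomised data exist on the safety of this drug class in these patients, so the events of most interest are those nobody has listed in advance.

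**Working it through.** The protocol article states no figure on this point, so the check is a comparison of text in two steps, followed by a short piece of algebra.

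**1. The two rules side by side.**

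| Question | Adverse events section | Protocol stopping rules |
|---|---|---|
| Which events enter? | Those already judged related, plus unanticipated problems | Serious and unexpected events, no condition on relatedness |
| When is relatedness judged? | Before reporting | During review, with DSMB help |
| Compared by arm? | Not stated | Yes, for life-threatening or serious events |

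Both cannot hold for a serious event that the investigator rates unrelated: the right-hand column requires its review and the left-hand column excludes it.

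**2. Which events depend on the restriction?** Each kind of event can be traced through the rest of the plan.

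- *Potassium and creatinine:* measured at day 7 and weeks 6, 9, 12, 16, 20 and 24 in all participants (Spironolactone treatment, under monitoring of participants). No attribution is needed.
- *Breast pain and gynecomastia:* asked about at baseline and follow-up visits (same section). No attribution is needed to elicit them.
- *Study drug discontinuation:* the prespecified safety and tolerability endpoint (Study endpoints), compared by Fisher exact test (Study analysis). Its potassium and creatinine components are thresholds; only the component for other side effects involves judgement.
- *Death, transplantation, right heart failure hospitalisation:* components of clinical worsening (Study endpoints), counted whatever their cause.
- *Unanticipated problems:* reported within 7 days.
- *Everything else:* syncope, falls, hospitalisation for other reasons, and hypotension or volume depletion when rated unrelated. For these the article gives no stated route except the related-only rule and the DSMB's periodic review, whose content it does not define.

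The gap is therefore the last line only.

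**3. What a related-only rule does to that remainder.** Let p1 and p0 be the true event proportions on spironolactone and placebo, and q the fraction judged related, assumed equal in both arms because assignment is double-blind.

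- Reported difference = q·p1 − q·p0 = q·(p1 − p0)
- Reported ratio = (q·p1)/(q·p0) = p1/p0
- With no true harm, p1 = p0 and the reported difference is 0.

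The absolute difference shrinks by the factor q, and there are fewer events from which to detect it. The ratio is unchanged and no false difference arises. The documents give none of p1, p0 or q. Across its possible range, q = 1 loses nothing and q = 0 loses the whole signal, so no single size can be stated.

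**The case against.** The strongest reply is that reporting is not recording. The sentence limits what is reported, and the paragraph after it concerns the Institutional Review Board. It may be a regulatory reporting rule, with complete recording and full DSMB tables described in the unshown full protocol. That reading is plausible and stands as a possibility. It does not remove the conflict, because the sentence as printed has no recipient and no exception for the DSMB or for serious events. If an IRB-only rule was meant, the text should say so.

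A second reply is that most of what matters is captured anyway. This is largely right and narrows the point to the remainder identified above. Hypovolemia (listed among the drug's main risks) and hypotension (mentioned under drug interactions) might also readily be rated at least possibly related.

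A reader might go further and infer three things that the documents do not support:

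- *That the DSMB cannot compare the arms.* It can, on laboratory values, discontinuations and clinical-worsening events, and it reviews symptom and outcome data every 6 months.
- *That the safety comparison as a whole is filtered by attribution.* The prespecified comparison is discontinuation, which is mostly laboratory-defined.
- *That visible potassium results make attribution differ by arm and so hide harm.* Nothing in the article shows this. If it happened, a raised potassium could as easily prompt more related ratings on spironolactone, which would exaggerate harm.

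**Conclusion.** The contradiction is real and should be resolved. Relatedness is an entry condition in one section and an outcome of review in another. Followed literally, the restriction may keep events judged unrelated out of the DSMB's comparison by arm when no other route captures them. The consequence is weaker detection of unexpected harm in that limited class of events, with no bias between arms if blinded attribution is equal in both.

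The conclusion assumes that the sentence means what it says for all recipients. If the full protocol confines it to IRB reporting, the fault reduces to unclear wording. The size of any loss depends on event rates and attribution habits that the documents do not give.

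**What to change.** Reconcile the two sections by amending the adverse event section to state that:

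- all adverse and serious adverse events during the 24-week treatment period are recorded in both arms;
- the investigator's relatedness rating is a data field and does not determine whether an event is recorded;
- all recorded events are tabulated by arm for the DSMB;
- the related-only limit applies to IRB reporting alone.

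Protocol stopping rules can then stand as written. The cost is a short text change and modest extra data entry at contacts already scheduled, for up to 70 participants. No new visits or tests are needed.

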## Discussion

Currently no published data exists from randomized clinical trials examining the safety and efficacy of MR antagonist therapy in early stages of PAH. Initiating therapy with spironolactone at an earlier stage of disease may improve PAH-associated vascular inflammation. This protocol describes the rationale, design and methodology of a randomized, double blinded, placebo-controlled pilot study in patients with PAH investigating the effect of early treatment with spironolactone on exercise capacity, clinical worsening and vascular inflammation *in vivo*.

### Trial status

We are in the recruiting phase.

## Abbreviations

ACE: angiotensin-converting enzyme; Cr: creatinine; DSMB: Data Safety and Monitoring Board; ECG: electrocardiography; eGFR: estimate glomerular filtration rate; HIV: human immunodeficiency virus; IL-1β: interleukin-1 beta; IL1RL1: interleukin-1 receptor-like 1; IL-6: interleukin-6; IL-7: interleukin-7; IL-8: interleukin-8; IPAH: idiopathic pulmonary arterial hypertension; IVCD: intraventricular conduction delay; K: potassium; labs: laboratory tests; LMM: linear mixed model; LV: left ventricular; MCP-1: monocyte chemotactic protein-1; MET: metabolic equivalent, MPH, miles per hour; MR: mineralocorticoid receptor; MRI: magnetic resonance imaging; NFκB: nuclear factor kappa B; NHLBI: National Heart, Lung, and Blood Institute; NIH: National Institutes of Health; NR: nuclear receptor; NSAIDs: nonsteroidal anti-inflammatory drugs; NT-proBNP: N-terminal pro-brain natriuretic peptide; NYHA: New York Heart Association; PAECs: pulmonary artery endothelial cells; PAH: pulmonary arterial hypertension; PBMCs: peripheral blood mononuclear cells; PCR: polymerase chain reaction; PH: pulmonary hypertension; PVCs: premature ventricular contractions; RNA: ribonucleic acid; RV: right ventricular; sCD40L: soluble CD40 ligand; sICAM-1: soluble intercellular adhesion molecule 1; sVCAM-1: soluble vascular cell adhesion molecule 1; TNFα: tumor necrosis factor alpha; VCO2: carbon dioxide production; VE: ventilation; VO2: oxygen uptake; WHO: World Health Organization.
